**Please advise patients:**

☐ To reduce salt intake, including pickles, soy sauce and other high-salt foods

☐ To quit smoking or to maintain non-smoking

☐ To drink less alcohol, with a daily intake of no more than one bottle to two bottles of beer or 50 g to 75 g liquor for male; no more than half a bottle to one bottle of beer, or 25 g to 50 g liquor for female.

☐ To reduce high-oil, high-fat food intake

☐ To do some simple rehabilitation or exercises

☐ To maintain a positive and healthy attitude.

1532

## Patient routine follow-up record keeping

**Acute symptom assessment**

Whether the patient has acute symptom that need referral?

- Stroke related symptoms
- Other symptoms
- Any acute situation that village doctor is unable to deal with

Specific symptoms

- ☐ 一侧肢体(伴或不伴面部)无力或麻木
- ☐ 一侧面部麻木或口角歪斜
- ☐ 说话不清或理解语言困难
- ☐ 双眼向一侧凝视
- ☐ 一侧或双眼视力丧失或模糊

**Medication adherence**

Morisky Medication Adherence Scale

- 1.1. 患者是否曾忘记服药?
- 1.2. 患者是否有不注意吃药的情况?
- 1.3. 当患者自觉症状改善时,是否曾停止服药?
- 1.4. 当患者服药后自觉症状更糟时,是否曾停止服药?
- 1.5. 从上一次随访到这次随访患者坚持服药所有药物的总天数。
- 1.6. 上传患者患者服药记录表

Days of taking medication

**Blood pressure**

2. 患者血压

| 收缩压 / 舒张压 | mmHg |
|-----------|------|
| 158 / 88  |      |
| 159 / 89  |      |
| 160 / 90  |      |
| 161 / 91  |      |
| 162 / 92  |      |

## Training & Quiz

**Training materials**

培训

学习资料 测试 培训记录

一、临床相关

1. 卒中中基本知识
  - 1.1 卒中中定义
  - 1.2 卒中中分类
  - 1.3 卒中中急症的表现
  - 1.4 卒中中病因及主要治疗方法
  - 1.5 卒中中的常规管理
2. 药物治疗
  - 2.1 血压管理
  - 2.2 抗血小板药物
  - 2.3 血脂管理
3. 非药物治疗
  - 3.1 非药物治疗原则
  - 3.2 戒烟
  - 3.3 限制饮酒
  - 3.4 减盐

**Clinical related test**

临床相关测试 (村医必考)

为巩固培训内容,请您完成测试! 测试包括10道题,需要在20分钟内完成。您至少需要答对8道题方可通过测试。

开始测试

其他测试,您可以自愿参与

生活方式相关测试 (选做) 开始测试

Village doctors are required to finish a quiz every three months. The quiz includes 10 questions and need to answer 8 questions correctly to pass the quiz.

**Training records and scores**

临床相关测试 分数 80

测试时间: 2016-6-14 耗时16分钟

下次完成测试时间: 2016-9-14至2016-9-28

### 9.3 Appendix A-3. Questionnaire for participants' survey at baseline and follow-up

**Note:**

Since we will use Qualtrics (electronic form) to collect data, the formatting of this paper version is not as consistent or as clear as it can be.

#### BASIC INFORMATION

|                                                                                  |                                       |
|----------------------------------------------------------------------------------|---------------------------------------|
| Date of the interview:    /    /                                                 |                                       |
| Participant initial: _____                                                       | Participant Project ID: _____         |
| Town: _____                                                                      | Village: _____                        |
| Sex: _____                                                                       | Year of birth: _____                  |
| Birth zodiacal animal: _____                                                     | Ethnicity: _____                      |
| *Marital status: _____                                                           | *Education: _____                     |
| *Occupation (before retirement): _____                                           | *Occupation (after retirement): _____ |
| Health insurance:                                                                |                                       |
|  Xingtai urban and rural resident basic health insurance |                                       |
|  Special non-communicable disease reimbursement          |                                       |
|  other _____                                             |                                       |
|  Do not have any health insurance                        |                                       |

#### HOUSEHOLD/FAMILY INFORMATION

Household size (how many people living in the household) and relationship: \_\_\_\_\_

Family income (yearly total):  
<10K <20K <30K <40K 50K 60K 70K 80K 90K >100K >150K

Does your family own a TV? If so, when purchases? Price then in RMB? \_\_\_\_\_

Does your family own an automobile (not agricultural vehicle)? \_\_\_\_\_ If yes, make model? \_\_\_\_\_

Do you have a phone? ☐basic phone ☐smart phone ☐no phone

If you have a phone:

Do you know how to send a text message? ☐Yes ☐No

Do you know how to read a text message? ☐Yes ☐No

Do you know how to use any APP such as Wechat? ☐Yes ☐No

Do you share a phone with your family member? ☐Yes ☐No

#### MAIN FAMILY HEALTH CAREGIVER

Who is your main family health caregiver? \_\_\_\_\_

Do you need his/her care? ☐Yes ☐No

How often does he/she remind you to take medicines? ☐Never ☐Seldom ☐Sometimes ☐Often ☐Always

Can his/her healthcare meet your needs?

Please enter the participant ID again: \_\_\_\_\_

#### STROKE-RELATED INFORMATION

When were you first diagnosed with stroke (only those diagnosed by county-level hospitals and or above)?

Year: \_\_\_\_\_ Month: \_\_\_\_\_ Type: \_\_\_\_\_ Diagnosed by/at: \_\_\_\_\_

Have you had recurrent stroke since then (only including episodes requiring a visit to or hospitalization at county-level hospitals or above)? How many times?

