Data on hospitalization and recurrence of stroke will be collected through extracting the data from county medical insurance system and death record system. Data on hospitalization will be extracted every month from the medical insurance system, which includes the reason and duration of the hospitalization. Death data will be extracted through the death report from the local CDC and verified through a smartphone-based shortened version of verbal autopsy survey administered by county project officer to family members of dead participants in this study. The survey has been proved to be feasible and acceptable in rural north China. Respecting the culturally appropriate grieving period, the interview will be conducted at the sixth and twelfth month after initial of the intervention. **Table 2** shows the overall data collection procedures based on SPIRIT guideline.

803 Table 2. The schedule of enrollment, intervention and assessments

|                                                         | STUDY PERIOD |                     |                              |                                                                                       |       |       |      |       |                      |
|---------------------------------------------------------|--------------|---------------------|------------------------------|---------------------------------------------------------------------------------------|-------|-------|------|-------|----------------------|
|                                                         | Enrollment   | Baseline Assessment | Allocation of treatment arms | Post-allocation                                                                       |       |       |      |       | Close-out Assessment |
| \TIMEPOINT                                              | -3 mon       | -2 mon              | 0 mon                        | 0 mon                                                                                 | 3 mon | 6 mon | 9mon | 12mon | 13 mon               |
| ENROLMENT:                                       |              |                     |                              |                                                                                       |       |       |      |       |                      |

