#### Exploratory outcomes

|                                              |                                                                                                                                                                                                                                                           |                                                                                                                          |
|----------------------------------------------|-----------------------------------------------------------------------------------------------------------------------------------------------------------------------------------------------------------------------------------------------------------|--------------------------------------------------------------------------------------------------------------------------|
| Stroke recurrence                            | Participants self-reported whether they had experienced stroke events during the 12-months follow-up period.                                                                                                                                              | Binary as experienced a stroke event vs. not experienced a stroke event                                                  |
| Degree of Disability (Modified Rankin Scale) | Participants' degree of disability evaluated based on assessors' observation and participants' self-reported symptoms or disability. A score ranged from 0 (no symptoms) to 5 (severe disability). A score of $\leq 2$ indicates functional independence. | Binary as score 0-1 (no symptoms at all or no significant disability despite symptom) vs (moderate to severe disability) |
| Stroke-related hospitalization               | Participants self-reported whether they were admitted in the hospital due to stroke event.                                                                                                                                                                | Binary as hospitalized due to stroke vs. not hospitalized due to stroke                                                  |

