| 1.1 Do patients present with any of the following symptoms or conditions that may need immediate referral:
 1 Symptoms of stroke during acute period: limb (with or without facial) weakness or numbness on one side; face numbness or mouth askew on one side; unclear speech or aphasia; both eyes gazing at one side; loss of vision of one or both eyes or being blurred; vertigo with vomiting; severe headache, vomiting rarely seen previously; disturbance of consciousness or convulsions; comprehensive cognitive impairment, such as reduction or loss of memory;
 2 Other acute symptoms: chest pain, palpitation, shortness of breath, failing to supine, decreased urine volume (less than 400 ml within 24 hours)
 3 Others: Any other symptoms that the village doctors cannot handle, for example: pregnant women or any other acute or severe symptoms
1.2 Patient's blood pressure: systolic pressure _____ mmHg /diastolic pressure _____ mmHg
End the follow-up and refer the patients to upper level hospitals if needed.                                                                                                                                                                                                                                                                                                                                                                                                                                                                                                                                                                                                                                                                                                                                                                                                                                  |

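### The printed stroke-recurrence question runs from the first-ever stroke and is undated, so it does not match the 12-month outcome in Table 4, and no rule says how one is derived from the other

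*Combined protocol and SAP*

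**What the plan says.** In Table 4 (section 7.3), stroke recurrence is an exploratory outcome defined as follows: "Participants self-reported whether they had experienced stroke events during the 12-months follow-up period". It is specified as "Binary as experienced a stroke event vs. not experienced a stroke event". The exploratory analysis paragraph of section 7.3 then estimates a risk ratio by modified Poisson GEE.

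The instrument is Appendix A-3 (section 9.3), titled "Questionnaire for participants' survey at baseline and follow-up". Under Stroke-related information it asks when the first stroke was diagnosed, and then: "Have you had recurrent stroke since then (only including episodes requiring a visit to or hospitalization at county-level hospitals or above". A second question follows: "How many times". There is no date field for any recurrence, and no separate 12-month wording is printed.

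Other sources are named. Section 5.6 states: "Data on hospitalization and recurrence of stroke will be collected through extracting the data from county medical insurance system and death record system". It adds that admissions are pulled monthly with the reason. Section 5.7 and Table 3 list both the questionnaire and insurance records for recurrence. A-3 also has an admissions item covering the preceding 12 months, with a diagnosis for each stay. Section 6.4 says the two surveys are linked by study ID. No section says how the 12-month yes/no variable is built from these sources, or which prevails when they disagree.

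**The concern.** The outcome has a 12-month window, whereas the question's window opens at the first-ever stroke. The trial enrols prevalent stroke survivors, so some will have had a recurrence before they joined. Such a person can truthfully answer yes at the 12-month survey without having had a new stroke.

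If those answers became the outcome, events fixed before randomization would be added to both arms. They raise the apparent risk in each arm and shrink the relative difference. Chance imbalance in old recurrences between the arms could also move the ratio in a single trial either way. Without a written rule, the analyst has to choose a derivation once the data are in hand, and the most direct choice is the biased one.

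**Working it through.** **The plan's own figure.** The documents contain no calculation for recurrence. The only design calculation is the power for systolic blood pressure in section 5.3, stated as 83%. With 23 villages per arm and 24 patients per village, the design effect is 1 + (24 − 1) × 0.04 = 1.92. The effective size per arm is 23 × 24 / 1.92 = 287.5. For a 5 mmHg difference and an SD of 20, a noncentral t with 44 degrees of freedom gives 83.4%, so the figure reproduces. It does not depend on recurrence.

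**Inputs for the illustration**

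- p0, the 12-month control risk: 11.2%. This is the first-year recurrence rate in section 1, used here only as a stand-in. It is a background figure, not a rate for this cohort.
- RR, the true risk ratio: 0.70 (assumed).
- q, the share with a recurrence before enrolment: 10% to 40% (assumed; the documents give none). Randomization makes it equal across arms in expectation.
- New recurrence is taken as independent of earlier recurrence.

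**Formula, if a raw yes is used as the event**

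Observed control risk = q + (1 − q) × p0

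Observed intervention risk = q + (1 − q) × p0 × RR, where p0 × RR = 0.112 × 0.70 = 0.0784

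| q | Control | Intervention | Observed RR | q / control risk |
|---|---|---|---|---|
| 0% | 0.112 | 0.078 | 0.70 | 0% |
| 10% | 0.10 + 0.90 × 0.112 = 0.201 | 0.10 + 0.90 × 0.0784 = 0.171 | 0.85 | 50% |
| 20% | 0.20 + 0.80 × 0.112 = 0.290 | 0.20 + 0.80 × 0.0784 = 0.263 | 0.91 | 69% |
| 30% | 0.30 + 0.70 × 0.112 = 0.378 | 0.30 + 0.70 × 0.0784 = 0.355 | 0.94 | 79% |
| 40% | 0.40 + 0.60 × 0.112 = 0.467 | 0.40 + 0.60 × 0.0784 = 0.447 | 0.96 | 86% |

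The last column is the share of control-arm yes answers given by people who could already have answered yes at baseline.

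**Sensitivity.** With a true ratio of 0.50 and the same p0, the observed ratios are 0.75, 0.85, 0.90 and 0.93. With a true ratio of 0.70, p0 from 5% to 15% and q from 10% to 40%, the observed ratio runs from 0.83 to 0.98.

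**After correction.** Limiting the item to the follow-up period, or correctly subtracting the baseline count, sets q to 0 and returns the true ratio.

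**The case against.** A reader might infer that earlier recurrences are in fact coded as trial events. The documents do not support that. Table 4 governs the outcome and excludes them, and nothing says that raw answers are used. The plan also collects material that could remove them: the count asked at baseline and again at 12 months, the link by study ID, the 12-month admissions item, and the monthly insurance extracts. This stands, and it makes the point conditional. It does not close the gap. Table 4 names self-report alone. The admissions item misses recurrences seen without an admission, which the A-3 question explicitly counts, and the insurance extraction is described for admissions. No rule brings these sources together.

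The fielded form may also differ from the printed one. A-3 carries this note: "Since we will use Qualtrics (electronic form) to collect data, the formatting of this paper version is not as consistent or as clear". The note concerns formatting, not recall periods. Still, the printed form departs from the plan elsewhere: it shows an eight-item adherence scale where section 5.7 specifies four items, and it has no date of last stroke although a subgroup in section 7.4 needs one. So the 12-month wording actually used is uncertain. That argues for stating it, and bounding the question is practicable: the post-trial form in Appendix B2 limits recurrence to the past year and records year and month.

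A reader might further infer arm-dependent detection, because A-3 counts only episodes at county level or above while the intervention visit record instructs: "End the follow-up and refer the patients to upper level hospitals if needed". The documents do not carry this far. Referral is conditional, the record's list of places visited includes township hospitals, and section 5.1 says most patients with urgent stroke events already receive acute care at county level or higher. The size cannot be derived. Dropping the facility criterion could itself add bias, because intervention doctors screen for stroke symptoms every month.

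**Conclusion.** The mismatch between instrument and outcome is on the page: an undated question reaching back to the first stroke, set against an outcome confined to the 12-month follow-up, with no derivation rule between them. Whether it biases the result depends on the derivation used. Uncorrected use would move a true risk ratio of 0.70 to between 0.85 and 0.96, given an 11.2% control risk and an assumed 10% to 40% with an earlier recurrence; using the baseline count or dated records properly would avoid this.

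The direction towards 1 holds on average. The size rests on assumed values for the prior-recurrence share and the true effect, and on a background rate borrowed as the control risk. The outcome is exploratory at one year, and the primary analysis of systolic blood pressure is untouched. The change is worth making because it costs almost nothing and settles the derivation before the data are seen.

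**What to change.** **If the 12-month form can still be set:** in that version of A-3, ask whether the participant has had a new stroke since the baseline interview, and record the month and year of each. Keep the existing facility criterion. The cost is one reworded question and a date field.

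**If the printed item was already used:** state in Table 4 that an event is an increase in the number of recurrences reported between baseline and 12 months, not a yes at 12 months. Cross-check it against the 12-month admissions item in A-3 and the monthly insurance extracts in section 5.6, and say which source prevails when they disagree. The cost is a short derivation rule on data already collected. The downside is recall error in the difference between two reported counts; reporting how many participants give a lower count at 12 months than at baseline would show how large that error is.

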#### COMORBIDITY

Have you been diagnosed by county or higher level hospitals the following: Yes, No, don't know

Heart disease \_\_\_\_\_

Hypertension \_\_\_\_\_

Diabetes \_\_\_\_\_

Cancer (any type) \_\_\_\_\_

Respiratory disease (any type) \_\_\_\_\_

Renal disease \_\_\_\_\_

Any other serious diseases? \_\_\_\_\_

#### HOSPITALIZATION

During the past 12 months, have you been hospitalized? \_\_\_\_\_

If yes, how many times have you been discharged by the hospital? For each admission, please list the days spent in the hospital and for what conditions and total costs:

\_\_\_\_\_ times

| Admission no.          | Days spent in hospital | Diagnosis (conditions for which admitted) | Total costs (RMB) |
|------------------------|------------------------|-------------------------------------------|-------------------|
| 1                      |                        |                                           |                   |
| 2                      |                        |                                           |                   |
| 3 (add more if needed) |                        |                                           |                   |

#### VILLAGE CLINIC

How often did you visit the village clinic? ☐ once a week or more ☐ 2~3 times per month ☐ once per month ☐ once per two months ☐ less than once per two months

What are your main reasons of visiting the clinic? ☐ measure blood pressure ☐ buy medicine ☐ counseling

On average, how many minutes did the village doctor spend with you each time? \_\_\_\_\_

How many times did the village doctor measure your blood pressure in the past one month? \_\_\_\_\_

#### BLOOD PRESSURE

Please measure the participant's blood pressure.

Reading #1: \_\_\_\_\_ / \_\_\_\_\_ / Heart rate \_\_\_\_\_

Did you take any antihypertensive drugs today? ☐ Yes ☐ No

If yes:

When did you take the medicine?

Did you take the medicine for 5 or more days in the past one week? ☐ Yes ☐ No

Compare with the medicine you took in the past week:

The amount of the medicine you took today are ☐ more ☐ same ☐ less

The type of the medicine took today are ☐ same ☐ different

**MEDICATION USE:**

Ask the following set of questions for aspirin, anti-hypertensive medicine, and lipid-lowering medicines for the past 12 months:

Have you been prescribed (been told by a doctor that you should take) aspirin during the past 12 months? \_\_\_\_ If yes, answer the following questions:

How many months have you taken aspirin tablets during the past 1 year?

Less than 2 months      2-8 months      9-11 months      Every month

How many days usually in a month did you take it as prescribed?

≥25 days      20-24 days      15-19 days      ≤14 days

Who prescribed the aspirin?

Self-prescribed    Zang doctor    Village doctor    Specialist

Where did you buy the aspirin?

Village clinics      Township center      County hospital

If not taking it more than 25 days a month, also ask:

Reason you did not take it as prescribed?

Expensive    Forget    No effect    Side effects    Others, please specify \_\_\_\_\_

*Instruct patients to bring ALL medicines they are currently taking in their original bottle/case/form.*

Have you taken any medication for your stroke or hypertension problems(s) during the past 1 month? If yes (or not sure what the med is for), fill in the form below:

| Medicine (brand name) | Use daily?
(≥25days in the last 30 days)              | Prescribed by village doctor?                            |
|-----------------------|----------------------------------------------------------|----------------------------------------------------------|
| 1.                    |  Yes  No |  Yes  No |
| 2.                    |  Yes  No |  Yes  No |
| 3.                    |  Yes  No |  Yes  No |
| 4.                    |  Yes  No |  Yes  No |
| 5.                    |  Yes  No |  Yes  No |

